### 2.4. Participants

#### 2.4.1. Eligibility

The participants’ inclusion criteria are as follows: (1) Chinese people who have mild ID (i.e., assessed in their most recent psychological report), (2) aged 18 or above, (3) able to master basic comprehension and verbal communication skills and (4) willing to complete the entire intervention. Those who demonstrate severe challenging behaviors will be excluded. Inclusion criteria for caregivers include the following: (1) main family caregivers identified by the participants with mild ID, (2) able to understand Cantonese or Chinese and (3) willing to complete the entire intervention.

#### 2.4.2. Recruitment of Participants

The participants with ID and their caregivers for all arms of the study will be recruited from five non-governmental organizations (NGOs) that provide adult services for people with ID. To achieve diversity in the study samples, the NGOs joining the present study are located in different districts in Hong Kong and currently provide diverse services include community support services, vocational training, employment services and residential services for adults with mild ID. Service users in residential settings have weekly home leaves and they would keep communications and interactions with their families. In addition, service providers reflect that they prefer open recruitment across different settings to recruitment from the same setting. Therefore, no specific service setting is excluded from recruitment. The social workers of the individual organizations will recruit eligible participants and their caregivers based on the inclusion and exclusion criteria for the study. It is known that offering an incentive (e.g., shopping vouchers) to participants upon completion of study is increasingly seen as good practice internationally. However, this study is not able to offer the incentives for the participants since the grant’s budget did not cover this item. Alternatively, the research team is producing additional promotional material (i.e., videos) to facilitate better recruitment. Using lively scenarios and layman language, the videos highlight that participants may benefit from the group intervention itself and their potential contributions to the service development.

### 2.5. Recruitment of Group Facilitators and Co-Workers

The group facilitators and co-workers responsible for the delivery of the group-based SD enhancement intervention are staff members (i.e., registered social workers and direct support workers) of the five participating NGOs. They must have received three sessions of training on the intervention provided by the research team and agree to participate in ongoing group supervision (see Section 2.10 for details).

### 2.6. Randomization

A computerized random number generator in Microsoft Excel is used to allocate participants into the different arms of the study. A research assistant from the research team will undertake the randomization, and the randomization results will be provided to the social workers of the participating NGOs. They are then responsible for contacting the participants, securing their consent and informing them of the session schedule.

Pre-group interviews will be conducted after the randomization. The objective of the pre-group interview is to enhance participants’ understanding of the study’s objectives and the schedule of the intervention groups, and to help group facilitators to familiarize themselves with the learning characteristics and group experience of the individual participants.

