## 2. Materials and Methods

### 2.1. Study Design, Aims and Hypotheses

This study is a randomized controlled trial (RCT), where adult participants with mild ID and their caregivers are randomized into three arms: (1) self-determination enhancement group (SD group), (2) self-determination enhancement PLUS group (SD-PLUS group) and (3) leisure activity group (comparison group, hereafter called leisure group). SD-PLUS is the only group to include caregivers during the intervention. There will be three assessment points: pre-test (T0), post-test (T1) and follow-up (3 months later) (T2); see Figure 2 for a diagrammatic representation of the study’s design structure. To ensure equity of access to a potentially effective intervention, participants in the leisure group will receive the same SD group intervention following completion of all the assessments for the intervention arm. The study protocol was approved by The Survey and Behavioral Research Ethics Committee of The Chinese University of Hong Kong (reference no.: SBRE-18-234) and the trial was registered in the ClinicalTrials.gov Protocol Registration (registration no.: NCT05167929).

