### 2.2. Ethical Concerns

Written consent will be sought both from the adult participants with mild ID and their caregivers. People with ID should be accorded as much respect as any other members of the population in terms of their having the autonomy to decide whether or not to participate in research [63]. In addition, this study is concerned with self-determination, and therefore the process of participation is itself a manifestation of self-determination for the participants. Additional measures suggested by the International Handbook of Applied Research in Intellectual Disabilities [64] will be adopted as follows: (1) An individual consent session will be arranged for every potential participant. The content of the consent form will be presented to the participants using plain language and incorporating pictures as visual cues. The participants will then be asked to sign the consent form. (2) A passive consent form will also be used to give dual protection to participants’ rights. Once the participants have signed the consent form, they will then be asked to give consent to us to contact their parents or guardians. Passive consent will then be sought from the parents or guardians.

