### 2.7. Data Collection Schedule

Demographic characteristics and baseline data about the participants will be collected before the group intervention commences (T0). Within one month following the completion of the intervention (T1), participants will be invited to complete the same scales used to collect baseline data (see Section 2.11) to measure any immediate effects. Three months after completion of the intervention, the same study cohort will be invited to complete the scales (T2), so as to measure the sustained intervention effects (see Figure 2). Participants of the SD groups and SD-PLUS groups will also be invited to complete the Self-Determination Action Plan at the end of the intervention. To ensure data quality, the individual face-to-face interviews will be conducted by interviewers who are trained in interviewing skills for people with ID.

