### 2.12. Statistical Analysis

Analyses of the outcomes will be performed using the intention-to-treat principle; this method is used to avoid the effects of crossover and drop-out in clinical research. Parameters for those who withdraw will be treated using maximum likelihood estimation (i.e., the full information maximum likelihood method). This method produces approximately unbiased results across a variety of parameter estimates, particularly with a small sample size [69]. Prior to all hypotheses testing, this study will conduct a Chi-square test and a *t* test to assess whether or not the sociodemographic characteristics and the baseline conditions of the participants with ID are different among the groups. Analyses of treatment outcomes will be conducted using hierarchical linear modelling (HLM), which is suggested to have more flexible data requirements (dealing with the missing data), and stresses individual change over group differences. Moreover, the HLM analysis is able to identify differences between conditions through the presence of a significant time x treatment interaction term. To examine the magnitude of change in the three groups at post-test and follow-up, effect size statistics will be calculated using Cohen’s d [70]. Finally, regression analyses will be performed to examine the relationships between changes in self-determination competencies and personal well-being among the participants with ID.

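### Section 2.6, read plainly, has consent secured after the allocation is disclosed, and T0 may follow it too, so refusal that differs by arm can bias the between-arm comparisons

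*Protocol article*

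**What the plan says.** All references are to the protocol article.

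- **Section 2.6 (Randomization).** A research assistant randomises, then "the randomization results will be provided to the social workers of the participating NGOs". The next sentence reads: "They are then responsible for contacting the participants, securing their consent and informing them of the session schedule". The section continues: "Pre-group interviews will be conducted after the randomization".
- **Section 2.4.2 (Recruitment).** The same group of staff recruits: "The social workers of the individual organizations will recruit eligible participants and their caregivers based on the inclusion and exclusion criteria for the study".
- **Section 2.2 (Ethical Concerns).** "An individual consent session will be arranged for every potential participant". The participant signs, then agrees to contact with parents or guardians, whose passive consent is sought next. None of these steps is placed before or after randomisation.
- **Section 2.4.1 (Eligibility).** Willingness to complete the whole intervention is an inclusion criterion for participants and, separately, for caregivers.
- **Section 2.7 (Data Collection Schedule).** "Demographic characteristics and baseline data about the participants will be collected before the group intervention commences (T0". Nothing ties T0 to the moment of allocation.
- **Sections 2.1 and 2.9.2.** "SD-PLUS is the only group to include caregivers during the intervention", and those caregivers are required to attend four sessions.
- **Section 2.12 (Statistical Analysis).** "Analyses of the outcomes will be performed using the intention-to-treat principle", with full information maximum likelihood for those who withdraw and a time-by-treatment term in a hierarchical linear model as the test between conditions.

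**The concern.** Randomisation protects a comparison only for the people who were committed to the trial before anyone knew their arm. If consent comes after the allocation is disclosed, each arm consists of those who agreed to that arm. The three arms ask different things of the family, so those who agree may differ from arm to arm.

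Hypotheses 3 and 4 are the most exposed. They compare SD-PLUS with SD in order to isolate the caregiver component, and caregiver attendance is the very demand that separates those two arms at the point of consent. Hypotheses 1 and 2 are exposed too, because the leisure arm offers no self-determination content during the trial.

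There is a second route. Both main outcomes are self-reported by participants. If T0 is taken after people have learned their arm, the baseline itself may move, and the time-by-treatment contrast is measured from that baseline.

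**Working it through.** The protocol gives no figure on this point, so there is none to reproduce. The check sets the sections side by side and then works through what could bias the planned contrast.

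**1. Order of consent and allocation.** Section 2.6 gives the sequence: randomise, hand over results, contact participants, secure consent, inform them of the schedule. Section 2.2 says how consent is taken but not when. Sections 2.4.1 and 2.4.2 give a willingness criterion and name the recruiters, but record no signed consent at that stage. No visible section places consent before allocation.

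**2. Position of T0.** Section 2.7 requires only that T0 precede the groups. A T0 interview needs a consenting participant, so if consent follows allocation, so does T0. This is an inference that rests on step 1.

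**3. Difference in demand.** Caregiver sessions required: SD-PLUS four, SD none, leisure none. Refusal after allocation therefore has a reason to differ by arm.

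**4. What the analysis can recover.** Full information maximum likelihood uses whatever a person has contributed. Someone who refuses at the consent step has no T0, T1 or T2 value and so contributes nothing. The 15% allowance in Section 2.3 describes drop-out as low attendance or incomplete questionnaires, and does not mention refusal between allocation and consent.

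**5. Algebra of the bias.** Let p_A and p_B be the refusal proportions in two arms. Let g0 and g1 be the mean of consenters minus the mean of refusers at T0 and at T1 (or T2), in SD units, equal in both arms, with no treatment effect.

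- Consenters minus all randomised, within an arm: p × g.
- Shift in the arm difference at T0: (p_A − p_B) × g0. At T1: (p_A − p_B) × g1.
- Shift in the difference in change: (p_A − p_B) × (g1 − g0).

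Assumed refusal, not from the documents: 20% in SD-PLUS and 5% in SD, so p_A − p_B = 0.15.

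| Assumed g0 | Assumed g1 | Level shift at T1 | Shift in change |
|---|---|---|---|
| 0.5 | 0.5 | 0.15 × 0.5 = 0.075 | 0.15 × 0 = 0 |
| 0.5 | 0.8 | 0.15 × 0.8 = 0.12 | 0.15 × 0.3 = 0.045 |
| 0 | 0.5 | 0.15 × 0.5 = 0.075 | 0.15 × 0.5 = 0.075 |

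For refusal gaps of 0.10 to 0.25 and g1 − g0 from 0 to 0.8, the shift in change runs from 0 to 0.25 × 0.8 = 0.20 SD. Equal refusal with the same selection gives zero.

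**6. Allocation-aware T0.** If knowing the arm moves the T0 difference between arms by s, and the shift does not persist to T1, the contrast in change moves by −s. The documents give no basis for a value of s.

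**7. Scale.** The plan's 105 evaluable participants give 105 / 3 = 35 per arm. For a simple two-sided z-test the standard error is √(2/35) = 0.239 SD of the quantity tested, ignoring clustering in groups. A shift of 0.05, 0.10 or 0.15 in those units raises the type I error from 0.05 to about 0.055, 0.070 or 0.096.

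**The case against.** The best defence has four parts.

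- **Willingness is screened.** Section 2.4.1 requires it of participants and caregivers, Section 2.4.2 recruits both for all arms, and Section 2.1 describes both as randomised. Dyads may therefore be identified and asked about willingness before allocation. This makes heavy refusal less likely, but a screening criterion is not signed consent and does not prevent refusal once the arm is known.
- **The word consent in Section 2.6 may mean agreement to attend the allocated group.** Section 2.2 speaks of potential participants, which would suit research consent taken at recruitment. This is possible, but no visible section says it. If it is the real procedure, Section 2.6 still needs a clarifying sentence.
- **Figure 2 is not available in the text reviewed and may show the order.** This is a fair limit on how firmly the position of T0 can be stated.
- **A level difference cancels.** The planned test is of change over time, so refusers who merely score lower throughout do not bias it. This stands.

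A reader might also infer more than the documents support:

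- That T0 certainly follows allocation. It is an inference from Sections 2.6 and 2.7.
- That T0 interviewers know the arm. Section 2.7 says only that they are trained. Awareness is stated for the social workers, and is likely for participants told their schedule.
- That every hypothesis is affected. Hypothesis 5 concerns SD-PLUS parents alone and is not a between-arm comparison.
- That SD-PLUS is favoured by a known amount. Its consenters may well have the more willing caregivers, but neither direction nor size follows from the text.
- That an arm would shrink by its refusers. No section says whether they are replaced.

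**Conclusion.** The point holds as a flaw in the stated sequence. On its plain reading, Section 2.6 discloses the allocation to the people who then seek consent, and no other visible section corrects this. T0 may follow allocation as well. Refusal can then differ by arm, refusers cannot be recovered by the planned analysis, and the intention-to-treat set need not be the randomised set.

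Hypotheses 1 to 4 can be biased on either of two conditions: refusers would have changed differently from consenters and refusal rates differ by arm, or knowledge of the arm moves self-reported T0. Hypotheses 3 and 4 are the most exposed. The size is unknown. Under the assumed inputs above it runs from nothing to 0.20 SD in the change contrast, and the upper end needs both a 25-point refusal gap and a 0.8 SD gap that opens entirely after baseline.

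It should be settled before enrolment, because no later analysis can restore people who refused after allocation.

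**What to change.** Reconcile Sections 2.2, 2.4.1, 2.6 and 2.7, and rewrite 2.6 and 2.7 in this order:

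1. Eligibility is confirmed.
2. The participant and the caregiver consent to any of the three arms, including the passive consent step in Section 2.2.
3. The T0 interview is completed.
4. The research assistant randomises those who have consented and been assessed.
5. The allocation is released to the social workers.
6. The pre-group interview is held and the schedule given.

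State that everyone who reaches step 4 counts as randomised and is analysed in the allocated arm. If research consent is in fact already taken at recruitment, say so and replace the word consent in Section 2.6 with one for agreement to attend. If T0 cannot be moved ahead of allocation, report refusals after allocation by arm, count everyone randomised, and keep T0 interviewers unaware of the arm.

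The cost is small: existing steps are re-ordered, with no new visits or staff. T0 falls slightly earlier relative to session 1, and the ethics committee must be notified.

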### 2.7. Data Collection Schedule

Demographic characteristics and baseline data about the participants will be collected before the group intervention commences (T0). Within one month following the completion of the intervention (T1), participants will be invited to complete the same scales used to collect baseline data (see Section 2.11) to measure any immediate effects. Three months after completion of the intervention, the same study cohort will be invited to complete the scales (T2), so as to measure the sustained intervention effects (see Figure 2). Participants of the SD groups and SD-PLUS groups will also be invited to complete the Self-Determination Action Plan at the end of the intervention. To ensure data quality, the individual face-to-face interviews will be conducted by interviewers who are trained in interviewing skills for people with ID.

### 2.8. Developing and Finalizing the Group Intervention Manual

The Manual of the Group-Based Self-Determination Enhancement Intervention is being developed by the research team, led by the author who is also the principal investigator. The group content is further being developed based on the study conducted in 2006 [65]. The manual includes three main sections: (1) theoretical and conceptual framework of the intervention, (2) principles (e.g., age-appropriateness and real-life learning) and instructional strategies (e.g., picture-based task analysis, flowchart, video-playing, role-playing and small group discussion) of the intervention and (3) the session plans (each session plan includes the objectives of the session, the rundown and time allocation, the detailed content of each section, remarks and practical tips for the group facilitator).

An expert panel will be formed to build the fidelity of structure. The panel will comprise three adults with mild ID, two caregivers of people with ID and two social workers who have more than 10 years’ experience working with people with ID. The panel members are invited to review the framework, content and specific instructional materials for the intervention. A user-friendly version is prepared for the members who have ID and they are invited to attend a practice session in which they try out the activities and exercises of the key sections. All members’ comments and views will then be collected and considered. The group manual will then be provisionally completed for the pilot study.

A trial intervention group will be conducted with eight group members, who meet the same inclusion and exclusion criteria of the later full-scale research study, and their parents. During this pilot study, the research team will test the intervention hardware (e.g., content accuracy, the effect of the multiple instructional strategies, time scheduling, etc.). The team will also accumulate soft skills to manage the software (e.g., ice-breaking and rapport-building skills, skills to manage group dynamics, skills to facilitate and motivate members’ learning, etc.). These soft skills can be transformed into fidelity to the process. The group manual will be further fine-tuned and then finalized according to the experience collected during the pilot study.

### 2.9. Intervention

#### 2.9.1. SD Group

The participants with ID allocated to the SD group will receive 10 weekly, 1.5-hour group sessions. Table 1 provides an overview of the two group interventions. Most sessions will start with a review of the home assignments and key content of the previous session (except session 1). The participants will learn new skills, using a case discussion, and then practice applying the new skills in their own situations. Home assignments will be assigned at the end of each session (except session 10); this will facilitate the participants to act on their own plans using their newly acquired knowledge and skills. There will be a two-week interval between session 6 and 7, to give the participants longer to implement their plans.

#### 2.9.2. SD-PLUS Group

The elements of REACH will be incorporated into the process for this group. Those participants with ID allocated to the SD-PLUS group will receive the same group content as those in the SD group, with the exception of session 8. This session will be renamed session 8+ for this group and will be a joint session with the participants with ID and their caregivers. The caregiver participants will be required to attend a four-session parallel group. The first two sessions are about what self-determination is and its importance, and using the REACH skills to support their children in implementing their goal pursuit plans. In session 3 (i.e., the joint session, which is also session 8+ of their children’s group), the caregiver participants will observe the performance of their children during the session and do dyadic exercises with them. After the joint session, the caregiver participants will attend the last session to review and share their experience and reflections in the joint session, and consolidate what they learned in the group. These four sessions are conducted bi-weekly, and each session lasts for 1.5 h (except the third session that lasts for 2 h) (see Table 1).

#### 2.9.3. Leisure Group

The participants with ID in this comparison group will attend 10 sessions of social activities that are unrelated to the SD enhancement model, with each session lasting for 1.5 h. For ethical reasons, the participants will be invited to receive the same content delivered in the same format as the SD group after the study is completed. This will be conditional on the SD group leading to significant enhancement on the primary outcome. If the SD-PLUS group proves to be effective, the participants will then receive the same content delivered in the same format as the SD-PLUS group. However, since the grant budget item does not cover this stage of data collection, the data would not be analyzed and reported.

### 2.10. Fidelity Check

The fidelity for the implementation of the intervention will monitored by three forms of measurement—for context, compliance and competence fidelity [66]. Context fidelity describes the necessary precursors to high-level performance. To ensure high context fidelity, all groups will be run by facilitators who are registered social workers with at least five years of experience working with people with ID. Their co-workers should also be registered social workers who have at least two years of experience working with people with ID, or direct support workers who have at least five years of experience. Before the start of the groups, all facilitators and co-workers will be required to attend a three-session training course conducted by the principal investigator and the research team to familiarize themselves with the content of the group manual and to learn specific skills for running the groups.

Compliance fidelity focuses on ensuring that the core intervention components are clearly described. To achieve this, all group facilitators and co-workers will be provided with detailed information, work sheets and props to be used in the group sessions. All group sessions will be videotaped. Regular group supervisions will be conducted by the principal investigator and the research team. During supervision, selected video episodes from the group sessions will be played back and discussed. Any difficulties encountered by the group facilitators and co-workers will be discussed, and it is expected that alternatives and solutions will be generated. The supervision sessions are also expected to lead to practice reflections and the accumulation of good practice methods among the facilitators and co-workers, through a mutual learning and support processes.

Competence fidelity measures how well the facilitators are performing the core intervention components of the evidence-based practice. A fidelity checklist is developed that covers the assessment of these areas: (1) instruction on the core self-determination components, (2) enabling the participants to participate and (3) facilitation of interactions among participants. Five experienced social workers who have worked with people with ID for more than 10 years, and who have no affiliation with this study, will be the fidelity reviewers. Video clips of three sessions from each group will be randomly selected, watched and rated by two reviewers who are randomly paired to achieve inter-rater reliability. Each reviewer will review 12 sessions from four groups.

